#### Effectiveness outcomes analyses

To assess *reach*, we will summarize participant-level indicators, including age, sex, blood pressure at enrolment, treatment for blood pressure at enrolment, and HIV history by clinic at the initial intervention visit. We will then estimate the percentage of patients with elevated blood pressure that receive the initial educational materials and lifestyle advice plus medication (numerator), from all patients identified with elevated blood pressure (denominator). Demographic and clinical characteristics between reached/not reached patients will be compared using chi-square / Fisher’s exact tests for categorical variables, and independent samples t-tests / Wilcoxon rank-sum tests for continuous variables.

To assess clinical impact of the intervention (*primary effectiveness outcome)*, we will examine differences in mean systolic blood pressure between intervention versus control clinics. We will estimate the effect of clinic-level intervention exposure (no intervention versus intervention by research staff) using mixed effects linear regression models. In addition to the standard stepped-wedge model outlined previously, we will include a random effect to account for correlation due to repeated measurements on participants. We will also include randomization strata, sociodemographic characteristics (age, sex, and immigration status), and clinical characteristics (prior treatment for hypertension, HIV regimen, CD4 count, and viral load) in our final multivariable model to obtain an adjusted estimate of the intervention effect.

The effectiveness analysis will use data from months 1–15 while censoring data from the first two months of intervention initiation (i.e., the transition period from control to intervention; see Table 1). This is to provide time for the intervention to impact patient behavior and medication initiation, thus giving time for blood pressure to be affected. We will follow an intention-to-treat approach in which data from individual patients will be analyzed according to the clinic intervention status at the time of measurement. Standard model diagnostic procedures will be used to evaluate model fit, and transformations will be applied (e.g., log transformation) as needed.

Similar to the analyses described for the implementation outcome, we will evaluate treatment heterogeneity between clusters (“horizontal”) and across periods (“vertical”). Additional subgroup analyses will evaluate treatment-effect heterogeneity by prior treatment for hypertension, HIV regimen, CD4 count, viral load, age, sex, and immigration status. We will present subgroup analyses with *P*-values from interaction tests as well as estimates of mean differences and 95% confidence intervals. In exploratory analyses, we will use a longitudinal cohort approach restricted to patients with two or more visits and with moderate-to-severe hypertension (i.e., systolic blood pressure > 160 mmHg or diastolic blood pressure > 100 mmHg) during the active intervention period. We will apply linear or logistic models, contingent on the distribution of the outcome, following the approach described for the primary implementation outcome analyses.

To assess *maintenance* of clinical effects, we will determine if the blood pressure improvements observed during the active intervention phase (research staff implementation, months 4–15) differ from those observed in the maintenance phase (clinic staff implementation, months 16–27). For this, we will use the same linear mixed model described for the primary effectiveness outcome and estimate the mean difference in systolic blood pressure between active intervention and maintenance periods. Results will be presented as a mean difference and 95% confidence intervals. If the mean is higher in the maintenance period and the 95% CI does not overlap zero, we will conclude that the improvements on systolic blood pressure were not maintained.

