**Methods:**

This protocol describes a type 2 effectiveness-implementation hybrid study conducted in nine primary care clinics in Johannesburg. The study will evaluate the effect of implementation strategies on guideline-recommended blood pressure assessment and management in HIV clinics and the effects of assessment/management on patient blood pressure. A stepped-wedge, cluster randomized study design was used to randomize clinics to the time at which they receive the implementation strategies and patient intervention. The implementation strategies tested include identifying and preparing care champions, changing record systems, conducting ongoing training, providing audit and feedback, and changing the physical structure/equipment. The patient intervention tested includes detection of elevated blood pressure, educational materials, lifestyle modification advice, and medication where needed. Implementation outcomes include adoption, fidelity (co-primary outcome), cost, and maintenance of the blood pressure assessment protocol in participating clinics, while patient outcomes include reach, effectiveness (co-primary outcome), and long-term effects of the intervention on patient blood pressure. These will be assessed via direct observation, study records, staff logs, medical chart reviews, and patient and healthcare worker surveys. To examine effects on the implementation (intervention fidelity) and effectiveness (patient blood pressure changes) co-primary outcomes, we will use the standard Hussey and Hughes model for analysis of stepped-wedge designs which includes fixed effects for both interventions and time periods, and a random effect for sites. Finally, we will examine the costs for the implementation strategies, healthcare worker time, and patient-facing intervention materials, as well as the cost-effectiveness and cost-utility of the intervention using study records, patient surveys, and a time and motion assessment.

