### Clinical intervention

The clinical intervention follows the recommendations from the South African Hypertension Society Guidelines [26] and includes the following components: (1) assessing blood pressure, (2) providing patient education, (3) providing brief lifestyle modification advice and, where needed, (4) providing blood pressure lowering medication (Fig. 2). Patient educational materials include color-coded posters placed in clinics and individual pocket-sized booklets explaining blood pressure levels (green = normal, yellow = high/elevated, red = very high), and what to do to lower or maintain blood pressure levels. Booklets also provide a longitudinal record for patients to self-monitor their blood pressure levels over time. All materials are available in English, isiZulu, isiXhosa, and Shona to cater for most of the populations clinics serve. All patients in these clinics receive this intervention regardless of the purpose of the visit or medical history unless they attend during the control period and do not return to the clinic.

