**EFFECTIVENESS EVALUATION**		
**Outcome definitions**	**Time points**	**Data source**
***Reach*** Percentage and representativeness of patients with elevated blood pressure and HIV that receive the intervention	At the initial / enrollment study visit (months 1–15)	• Study REDCAP form • Medical charts
***Effectiveness*** Primary clinical outcome: difference in mean systolic BP between the intervention and control periods	All visits in months 1–15, excluding the two months following intervention initiation	• Medical charts
***Cost-effectiveness*** Health utility of the intervention and direct medical costs of additional patient visits and/or hospitalizations	Control, active intervention (months 1–15), and maintenance periods (months 16–27)	• Quality of life (EQ-5D) patient questionnaire • Patient-reported cost survey • Study records
***Patient-level Maintenance*** Extent to which blood pressure improvements observed during the intervention phase are maintained	Active intervention (months 4–15) and maintenance (months 16–27) periods	• Medical charts • Study REDCAP form

*BP* blood pressure

*Adoption* will be determined as the percentage and representativeness of clinics that complete the blood pressure assessment protocol at the initial study step (i.e., did they roll out intervention? Yes/No). Intervention fidelity (*primary implementation outcome*) will be defined as the difference in percentage of patient visits with recorded blood pressure measurement between intervention and control periods. We will also keep track of adaptations made to the blood pressure assessment protocol via care coordinator notes and reports. Clinic-level *maintenance* of the intervention will be defined as the extent to which blood pressure continues to be assessed after the active intervention period ends based on medical chart reviews. We will also assess the normalization of the blood pressure assessment protocol using a 23-item questionnaire [32] healthcare workers will complete at the beginning and at the end of the maintenance period.

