*Reach* will be defined as the percentage and representativeness of patients with elevated blood pressure that receive educational materials and lifestyle modification advice / medication, among all patients with elevated blood pressure. Changes in patient blood pressure (*primary effectiveness outcome*) will be defined as the difference in mean systolic blood pressure between the intervention and control periods. Patient-level m*aintenance* of intervention effects will be defined as the extent to which blood pressure improvements observed during the active intervention period are sustained during the maintenance period.

The *cost* evaluation will examine direct medical costs for intervention delivery, including implementation strategies, patient-facing intervention materials, additional staff time required to deliver the intervention, and additional blood pressure medication. One-time costs for implementation strategies will be estimated from the study records. The additional time burden associated with integrating the blood pressure assessment protocol in participating clinics will be assessed using a time and motion assessment in a random sub-sample of 100 patients at each clinic during control, active intervention, and maintenance periods (900 per period; total *n* = 2,700). This assessment will collect data on the start and end time of different procedures during a patient’s journey through a routine clinic visit. Finally, this patient subsample will also complete a survey regarding medical expenditures for outpatient and inpatient care utilization during the last 12 months, and the EQ-5D quality of life questionnaire [33] to determine health utility.

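### The reach numerator in the analysis section requires medication, which the intervention gives only where needed, so fully served patients who need none count as not reached

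*Protocol article*

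**What the plan says.** Reach is described in three places in the protocol article.

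- **Table 3, Effectiveness evaluation:** "Percentage and representativeness of patients with elevated blood pressure and HIV that receive the intervention".
- **Outcome measures and definitions:** reach concerns "patients with elevated blood pressure that receive educational materials and lifestyle modification advice / medication, among all patients with elevated blood pressure", reported as a percentage and examined for representativeness.
- **Effectiveness outcomes analyses:** the percentage of patients with elevated blood pressure who "receive the initial educational materials and lifestyle advice plus medication (numerator), from all patients identified with elevated blood pressure (denominator". The same paragraph adds that "Demographic and clinical characteristics between reached/not reached patients will be compared".

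The intervention itself is described twice. The Clinical intervention section includes "providing brief lifestyle modification advice and, where needed, (4) providing blood pressure lowering medication" among its components, and the abstract lists "detection of elevated blood pressure, educational materials, lifestyle modification advice, and medication where needed". Both make medication conditional.

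The Study populations section limits the effectiveness evaluation population to adults with elevated blood pressure and known HIV, whether or not they already take blood pressure medication.

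**The concern.** The analysis section is the only place that labels a numerator and a denominator, so an analyst would most likely program from it. Its numerator joins medication to materials and advice without the qualifier used in the intervention description, and its denominator is not limited to patients who need medication. A patient for whom the clinic did everything the intervention asks, and who needed no medication, fails the definition.

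Two results would suffer. The reach percentage would understate delivery by an amount that depends on how many patients receive medication rather than on how well clinics performed. The comparison of reached with not-reached patients, meant to show how representative the reached group is, would mix delivery failure with absence of need for medication.

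**Working it through.** The article states no target, expected value or sample size for reach, so there is no figure to reproduce. The check sets the definitions side by side and then illustrates the consequence.

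**Step 1. Classify the same patients under each definition.** The slash in the outcome section is read here as *or*. Table 3 is read with the intervention as the Clinical intervention section describes it. All four patients received the educational materials.

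| Patient | Analysis section | Outcome section | Table 3 |
|---|---|---|---|
| Needs medication; advice and medication given | reached | reached | reached |
| Needs no medication; advice given | not reached | reached | reached |
| Needs medication; advice given, medication not | not reached | reached | not reached |
| Needs medication; medication given, advice not | not reached | reached | not reached |

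The second row is the point at issue: the analysis section disagrees with both other definitions. The last two rows show that the outcome section's slash is itself too loose to settle the matter.

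**Step 2. Bound.** Every patient counted under the analysis rule must have received medication. Reach is therefore at most the share of the denominator receiving medication, and the article does not give that share.

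**Step 3. Illustration.** Let *m* be the share of patients who need medication and *d* the share who receive every component they need. Assume that *d* is the same with and without need for medication, and that only those who need medication receive it. Neither *m* nor *d* is in the article; the values below are assumptions.

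- Analysis rule: reach = *m* × *d*
- Medication-where-needed rule: reach = *d*
- Fully served patients scored as not reached: (1 − *m*) × *d*
- All patients scored as not reached: 1 − *m* × *d*

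| *m* | Analysis rule, *d* = 100% | Analysis rule, *d* = 90% | Fully served share of the not-reached group, *d* = 90% |
|---|---|---|---|
| 20% | 20% | 18% | 72/82 = 88% |
| 40% | 40% | 36% | 54/64 = 84% |
| 60% | 60% | 54% | 36/46 = 78% |
| 80% | 80% | 72% | 18/28 = 64% |
| 100% | 100% | 90% | 0/10 = 0% |

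The medication-where-needed rule gives 100% and 90% in every row. The two rules agree only when every patient needs medication. In the last column, the rest of the not-reached group are true delivery failures, so the comparison is affected in part.

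**Step 4. Denominator.** Table 3 names HIV; the outcome and analysis sections refer to all patients with elevated blood pressure. Table 3 and the analysis section both place reach under the effectiveness evaluation, whose population is restricted to patients with known HIV. Consent for chart abstraction is described for that group only. In the wider triage population, the items listed are whether blood pressure was measured, its values, and whether materials were delivered; advice and medication are not among them. The natural reading is that all three places mean patients with HIV and elevated blood pressure.

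**The case against.** The strongest defence is that the analysis wording is shorthand. Table 3 refers to the intervention, the intervention gives medication conditionally, and an article condenses a fuller protocol in which the coding of a secondary outcome may be set out properly. That may well be the intent. But this is not a detail left out: the article states a numerator, and the numerator as stated conflicts with its own description of the intervention.

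Four stronger readings are tempting, and the article does not support them.

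- **The denominators contradict each other and differ by the proportion without HIV.** Context largely answers this, as shown in step 4. What remains is a small alignment of wording.
- **Reach is capped at the share needing medication.** The ceiling is the share *receiving* it. Patients already on treatment are eligible and their treatment at enrolment is summarised, but the article does not say whether existing treatment counts towards reach.
- **The reached versus not-reached comparison becomes purely one of severity.** Among patients who got everything they needed, the rule does separate by medication. Delivery failures also fall in the not-reached group, so the distortion is partial.
- **The 40% to 80% figures measure the error in this trial.** They are assumed values that show how the rule behaves.

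**Conclusion.** The point holds for the numerator. Read as written, the analysis section classes patients who received every component called for, but needed no medication, as not reached. Reach cannot then exceed the share receiving medication, and the reached versus not-reached comparison partly reflects need for medication. The size cannot be determined from the article. The illustration rests on the stated assumptions about need, equal delivery and who receives medication, and the discrepancy vanishes only if all patients need medication.

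Reach is a secondary outcome reported as a percentage with unadjusted group comparisons. Neither co-primary analysis uses the reached classification, and the sample size rests on systolic blood pressure. The correction should be made before reach is analysed, but it does not threaten the trial's main conclusions.

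**What to change.** Reconcile Table 3, Outcome measures and definitions, and Effectiveness outcomes analyses into one definition.

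- **Numerator:** count a patient as reached when educational materials and lifestyle advice were delivered and medication was provided where the study's existing protocol called for it. Report medication as a separate component as well.
- **Denominator:** as a minor alignment, say in the outcome and analysis sections that it is patients with HIV and elevated blood pressure, as in Table 3 and the Study populations section.

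While rewording, say how medication already being taken at enrolment is counted.

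The cost is wording only. Who needs medication stays with the study's existing protocol, and no clinical rule, primary analysis or sample size changes.

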#### Costing, cost-effectiveness and budget impact analyses

These analyses will concentrate on direct medical costs including costs for intervention delivery and costs for outpatient and inpatient health care utilization, taking roughly a public healthcare system perspective. Time of healthcare staff for implementing the intervention will be valued according to average gross salaries including fringe benefits. The change in hypertension medication cost will be monetarized by multiplying the volume of hypertension medication with average market prices for hypertension medication. We will describe raw absolute accrued costs for each cost category in the intervention and control periods and stratified for the control, active intervention, and maintenance period. Since there is no value set for South Africa, we will use an established scoring algorithm developed for a neighboring country [41] to translate EQ-5D health states into health utilities. We will assess cost-effectiveness as the incremental cost per mmHg reduction in systolic blood pressure and the cost-utility as the incremental cost per quality adjusted life year gained [42]. Uncertainty in incremental costs, utility, and cost-effectiveness/cost-utility will be assessed through non-parametric bootstrapping methods [43]. We will report the cost-effectiveness plane and the cost-effectiveness acceptability curve for different willingness to pay thresholds for a gain in one quality adjusted life year. We will also conduct rough extrapolations to assess the expected intermediate- and long-term budget impact on population level [44, 45]. For these analyses, we will follow the Consolidated Health Economic Evaluation Reporting Standards 2022 [46].

## Discussion

This study aims to examine whether context-specific implementation strategies improve the detection and management of elevated blood pressure among PWH in South Africa. We will test five implementation strategies designed through community-engaged formative work [21] using a type 2 effectiveness-implementation hybrid study [34] and a stepped-wedge cluster randomized design. These methods assure both internal validity for testing the effects of the implementation strategies and external validity by approximating the conditions of real-world HIV care. Finally, this study incorporates budget impact and cost-effectiveness analyses which will inform decision-makers of the potential costs associated with integrating guideline-recommended CVD preventive practices in HIV care.

Several policies and programs aimed at integrating non-communicable disease and HIV care have been rolled out in several Sub-Saharan African countries, but several challenges have hampered large-scale implementation [19, 20]. This study is among the first to systematically address implementation challenges in the South African HIV care system and will contribute evidence to inform large-scale integration of HIV-CVD care in this setting. Our study is part of a consortium of studies funded by the US National Heart Lung Blood and Sleep Institute focused on testing diverse implementation models to address CVD co-morbidities in PWH [47]. Another study that is part of this alliance is focused on testing practice facilitation to improve hypertension treatment in HIV care in Nigeria [48]. Similarly, a study in Mozambique is using a systems analysis and improvement approach to optimize the hypertension diagnosis and care cascade for PWH [49]. The studies in this alliance will contribute evidence on effective implementation models to promote the integration of HIV-CVD care in Sub-Saharan Africa.

This study employs diverse implementation research methods that ensure rigorous testing of our implementation strategies and advance implementation research in global settings. For instance, our study employs implementation theories, frameworks and methods to guide our formative work, intervention and strategy design, data collection, analyses, and interpretation. Hence, this study provides a dual opportunity to test these methods in the South African clinical context and learn about refinements needed for global settings and populations [50]. This study will also contribute to addressing implementation research gaps previously identified in HIV-CVD care integration in Sub-Saharan Africa [51] by employing a rigorous study design and reliable measures to answer research questions in low-resource, global contexts.

## Data Availability

Data sharing is not applicable in this manuscript since no datasets were generated or analyzed.
